## Abstract

**Background:**

Osteoporosis is becoming more prevalent in aging societies worldwide, and the economic burden attributable to osteoporotic fractures is substantial. The medications presently available to treat osteoporosis have side effects. Acupuncture is widely used for treating osteoporotic postmenopausal women because it is non-invasive and has fewer side effects, but the powerful clinical evidence for its efficacy remains insufficient. Our study intends to explore the effect of overall adjustment acupuncture (OA) in the treatment of postmenopausal osteoporosis (PMOP).

**Methods/design:**

This study is a randomized, sham-controlled, patient- and assessor-blinded trial and aims to evaluate the effect of OA in women with PMOP. We will recruit 104 women aged 45–70 years with a diagnosis of PMOP. Participants will be randomly allocated in a 1:1 ratio to the OA group and the sham acupuncture (SA) group. Both groups will receive real herbal medicine treatment as a basic treatment twice a day for 3 months, the OA group receives real acupuncture treatment and the SA group receives placebo acupuncture treatment (non-penetrating, sham skin-needle therapy, sham cupping). All patients will receive acupuncture treatment twice per week for 3 months. The primary outcome is bone mineral density (BMD) and the secondary outcomes include estradiol (E2), follicle-stimulating hormone (FSH), bone gla protein (BGP), bone alkaline phosphatase (BALP), total antioxidant capacity (TAC), advanced oxidation protein products (AOPP), PPARγ, β-catenin, FoxO3a levels, visual analog pain scale score (VAS), Traditional Chinese medicine (TCM) syndrome scores and quality of daily life score (QOL). Outcome measures will be collected at baseline, middle of the treatment (1.5 months), the end of treatment (3 months). The present protocol followed the SPIRIT guidelines and fulfills the SPIRIT Checklist.

**Conclusion:**

This study will be conducted to compare the efficacy of OA versus SA. This trial should help to evaluate whether OA can effectively prevent and treat PMOP by improving the estrogen levels of postmenopausal women. The mechanism is to improve the imbalance of osteogenic differentiation and lipogenesis of bone-marrow cells under oxidative stress.

**Trial registration:**

Chinese Clinical Trial Registry, ID: ChiCTR1800017581. Registered on 5 August 2018. URL: http://www.chictr.org.cn.

## Introduction

The high incidence and the associated pain and fractures of postmenopausal osteoporosis (PMOP) have seriously threatened many women’s physical and mental health, as well as their life quality. According to statistics, about one quarter of perimenopausal women will develop osteoporosis, and these women will lose bone mass rapidly within 5 years post menopause; the premenopausal loss is two to three times that of younger women [1].^.^The prevention and treatment of PMOP is directly related to the physical and mental health outcomes of most postmenopausal women, and this has great social and practical significance.

Postmenopausal osteoporosis is caused by a decline of ovarian function, rapid aging of the body, decreased estrogen levels, hyperabsorptive function, and compensatory enhancement of osteoblastic bone formation. All of these factors result in a high degree of bone metabolism. The ensuing state of negative balance eventually leads to a decrease in bone mass, destruction of bone microstructure, reduction of bone strength, and a type of systemic bone metabolic disease that is prone to fractures [2]. In recent years, it has been recognized that PMOP is caused by aging, and estrogen deficiency. As the basic pathogenesis of aging, oxidative stress plays an important role in the occurrence of related diseases. Estrogen is a powerful antioxidant, and increased accumulation of reactive oxygen species (ROS) induces oxidative stress, eventually lead to PMOP [3]. It is generally believed that with the increase of ROS and oxidative damage, the formation and survival of bone osteoblasts decreases, while osteoclastic differentiation and activity increase [4, 5]. Some researches show that acupuncture which is performed on the basis that conventional orally administered calcium improves bone density and serum estradiol levels in PMOP patients. The mechanism may be that acupuncture can increase estrogen levels and promote osseous calcium deposition, can affect the bone turnover in order to increase bone density [6]. Oxidative stress-mediated balance of the FoxO3a-β-catenin-PPARγ signal axis may play an important role in bone-marrow mesenchymal stem cells (BMSCs). β-catenin plays a central role in the regulation of osteogenic differentiation and osteoblast activity in the bone-marrow-fat environment [7].

At present, the prevention and treatment of osteoporosis (POP) mainly depends on pharmaceuticals, but there are certain side effects [8], and their long-term effect is unsatisfactory. Estrogen therapy, as a complementary replacement therapy for PMOP, has a long-term application with definite effects, but may often cause adverse events such as breast cancer or endometrial cancer [9]. The side effects of other medicines which are commonly used in clinical practice have also become increasingly prominent. Adverse reactions, such as atypical femoral fractures and mandibular necrosis, caused by the use of bipionate have also attracted increasing attention [10]. The findings have affected their acceptance by many patients. Therefore, it is significant to find a safe, effective, ecologically green, natural, and non-side-effect-causing treatment. Also, first-line clinical medicine is mostly focused on inhibiting the abnormally active bone resorption dominated by osteoclasts. Simply inhibiting osteolysis is difficult to fundamentally treat osteoporosis. The mature growth of osteoblasts is the basis of bone health, so we should pay more attention to the research on methods of promoting bone formation.

Acupuncture therapy is a important therapy for the prevention and treatment of chronic metabolic diseases in traditional Chinese medicine (TCM). The clinical treatment of acupuncture for this disease is mainly to strengthen the kidney and bones, while regulating the spleen and kidney. The clinical effect of acupuncture on this disease is definite, and it can significantly improve the symptoms of low-back pain, limb weakness and kidney deficiency caused by PMOP. Acupuncture can not only alleviate and improve clinical symptoms, such as pain, in patients with osteoporosis, but also can prevent osteoporosis by regulating the levels of endocrine hormones in the body, increasing bone density, and improving abnormal bone metabolism [11, 12].

The currently recognized principles of TCM treatment of osteoporosis are syndrome differentiation, overall regulation, prevention and treatment [13]. “Overall adjustment acupuncture” (OA) is a kind of acupuncture treatment based on TCM, which is an effective, systematic, comprehensive and multi-pathway treatment of osteoporosis. The OA is based on more than 20 years of clinical experience and experimental verification. It combines the main etiology and pathogenesis of osteoporosis with kidney and spleen deficiency. It involves a systematic process for osteoporosis and it combines acupuncture, moxibustion, and skin-needling organically to stimulate the meridian system such as those of the skin, collaterals, and meridians. According to the full regulation of this therapy, osteoporosis has been treated by improving clinical symptoms and patients’ quality of life through multiple channels [14]. During the early stages of clinical treatment, it was found that the OA method has a good effect on PMOP, but a systematic and comprehensive clinical study has not been conducted and, thus, its mechanism of action is not clear. This trial will study the efficacy, safety and mechanism of acupuncture therapy on PMOP. There are few reports on the treatment of PMOP by sham acupuncture (SA) as a control group. Our trial hypothesis is that overall regulation acupuncture treats PMOP by increasing the estrogen levels of postmenopausal women and improving the imbalance of osteogenic and adipogenic differentiation of BMSCs caused by oxidative stress in the human body.

## Methods/design

### Study design

This is a randomized, sham-controlled, patient- and assessor-blinded trial. A target sample of 104 participants will be recruited from the Acupuncture Clinic at the First Affiliated Hospital of Dali University and Yunnan Provincial Hospital of Traditional Chinese Medicine. The present protocol follows the Standard Protocol Items: Recommendations for Interventional Trials (SPIRIT) guidelines and fulfills the SPIRIT Checklist (Additional file 1). The trial flow chart is shown in Fig. 1. The protocol is in line with the principles of the Declaration of Helsinki and has been approved by Institution Review Board (IRB) of Yunnan Provincial Hospital and Traditional Chinese Medicine (approval no. 2018–003-01). This trial was registered at the Chinese Clinical Trial Registry (ChiCTR1800017581). Any changes which need to be made in the trial protocol will be communicated to all researchers, the Ethics Committees, and the trial registry. Written informed consent will be signed by each participant.

**Fig. 1 Fig1:**
[figure not shown]
Study flow chart

Participants who voluntarily sign the informed consent, and who are eligible for this study, will be assigned randomly to one of two groups (the acupuncture group or the SA group) in a 1:1 allocation. On the consent form, participants will be asked if they agree to the use of their data should they choose to withdraw from the trial. Participants will also be asked for permission for the research team to share any relevant data with people from the Dali University who are taking part in the research or from regulatory authorities, where relevant. The study participants were recruited competitively from two sites of the Acupuncture and Moxibustion Department of Yunnan Province Hospital of TCM and the First Affiliated Hospital of Dali University. A total of 104 postmenopausal women with osteoporosis were recruited via broadcast media, newspapers, posters, and the Internet homepages of the participating hospitals, as well as via advertisements placed in nearby welfare centers.

### Randomization and allocation concealment

For randomization, an independent, blinded statistician will generate random numbers using the SAS randomization program (version 9.4; SAS Institute, Inc., Cary, NC, USA). The manufacturer will supply the hospital with investigational treatments in consecutively numbered drug containers with identical packaging to conceal treatment allocation. Blinded researchers in each hospital will enroll and assign participants to one of the two study groups.

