### Sample size and blinding

According to the preliminary research [15], we hypothesize that the effective rate after OA is 77.8% and the effective rate after SA is 50%. The equation that we used for this was *α* = 0.05, *β* = 0.20 and we determined that a sample size of 42 patients in each group would be sufficient to detect the statistical difference between the two groups, allowing for a 20% withdrawal rate. We will plan to enroll a total of 104 participants with 52 participants in each group. According to the random number sequence generated by computer, the patients will be randomly divided into either the OA group or the SA group in a 1:1 ratio.

The participants, outcome assessors, study monitors, data managers, and statisticians will be blinded to treatment allocation. If possible, the study participants will be advised to avoid discussing the investigational treatments with other participants. Blinding will be maintained until the 104 participants have completed the study. The success of double-blinding will be assessed at the final visit. Due to the special nature of acupuncture, acupuncturists cannot be blinded to the treatment. The database will then be locked. An emergency code for each individual has been provided to the study researchers and will be disclosed only if it must be known whether a patient is receiving acupuncture treatment or SA in order to manage a serious adverse event.

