### Interventions

Both the OA and SA groups will receive acupuncture sessions for a total of 3 months. All the patients will receive herbal medicine twice a day for 3 months. The same physician (the Professor of Acupuncture in Yunnan Provincial Hospital and Traditional Chinese Medicine, who has 20 years of work experience) will slightly adjust the formula each week depending on the changes of the symptoms, pulse, and tongue coating of the patients (main herbal formula components are shown in Table 1). During the trial, patients will be classified by pattern differentiation: (1) spleen-kidney *Yang* deficiency will be given Yougui Pill; (2) liver-kidney *Yin* deficiency will be given Zuogui Pill; and (3) kidney deficiency and blood stasis will be given Bushen Huoxue decoction. Participants will be given all the herbs from the same hospital and the physician will instruct them how to decoct.

**Table 1 Tab1:** Main herbal formula selection

Pattern	Formula	Composition
Spleen-kidney *Yang* deficiency	Yougui Pill	radix rehmanniae preparata, cortex cinnamomi, cornu cervi degelatinatum, rhizoma dioscoreae, fructus corni, fructus lycii, radix angelicae sinensis, cortex eucommiae, semen cuscutae, radix morindae officinalis, rhizoma drynaria, rhizoma sparganii
Spleen-kidney *Yin* deficiency	Zuogui Pill	radix rehmanniae preparata, rhizoma dioscoreae, fructus lycii, fructus corni, radix achyranthis bidentatae, deerhorn glue, deerhorn glue, radix morindae officinalis
Kidney deficiency and blood stasis	Bushen Huoxue decoction	radix rehmanniae preparata, semen cuscutae, cortex eucommiae, fructus lycii, radix angelicae sinensis, fructus corni, cistanches herba, commiphora myrrha, radix angelicae biseratae, radix angelicae sinensis

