### Sham acupuncture (SA)group

The procedure and duration of treatment in the SA group will be identical to the OA group except for the needles (0.25 × 25 mm with a blunt tip, manufactured by Suzhou Medical Device Company in Suzhou, Jiangsu Province, China). The *Qixing* needle tips are wrapped in cotton (shown in Fig. 3) are blunt-tipped and there will be no skin penetration or manual stimulation, but at the same time cupping is applied to the skin with a small negative pressure compared to that in the OA group (show in Fig. 4).

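### The only stated means of concealing allocation, identical numbered drug containers, does not fit a trial whose arms differ in needling, tapping and cupping and not in any drug

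*Protocol article*

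**What the plan says.** The section on randomization and allocation concealment has three elements. An independent, blinded statistician generates the random numbers in SAS. Next, the trial treatments reach the hospital from the manufacturer in "consecutively numbered drug containers with identical packaging to conceal treatment allocation". Finally: "Blinded researchers in each hospital will enroll and assign participants to one of the two study groups". No other concealment method appears in the article.

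On drugs, the abstract states: "Both groups will receive real herbal medicine treatment as a basic treatment twice a day for 3 months". The Interventions section repeats this ("All the patients will receive herbal medicine twice a day for 3 months"). It adds that the formula follows the pattern diagnosis, that one physician modifies it weekly, that the herbs come from the same hospital, and that patients are shown how to decoct them.

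On what is randomised, the abstract says that "the SA group receives placebo acupuncture treatment (non-penetrating, sham skin-needle therapy, sham cupping"). The sham section opens with "The procedure and duration of treatment in the SA group will be identical to the OA group except for the needles", and then also describes cotton-wrapped skin-needle tips and a lower cupping pressure.

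The section on sample size and blinding says that acupuncturists cannot be blinded, and that "An emergency code for each individual has been provided to the study researchers", to be disclosed only when a serious adverse event requires it.

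**The concern.** Concealment protects the step before assignment: whoever decides that a patient is eligible and enters her must not know, or be able to guess, the arm she will get. Numbered, identical drug containers do this well when the container carries the treatment, as with active drug and matching placebo. The person enrolling hands over the next number without knowing its contents.

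In this trial someone must tell an acupuncturist which set of procedures to perform. If the stated device cannot carry that message, the article gives no account of how the message travels, who sees it, or when. If staff at either hospital could learn the next assignment before entering a patient, enrolment could become selective by arm. Randomisation exists to prevent that imbalance, and analysis cannot reliably repair it.

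This differs from patient and assessor blinding. The sham needles and devices address what patients and assessors perceive after assignment. They do not protect the decision to enrol.

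**Working it through.** No figure is involved, so the check sets the stated mechanism beside the description of the arms.

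1. **What a numbered drug container needs in order to conceal.** It must hold something that differs by arm, look the same in both arms, and be prepared in advance against the randomisation list.

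2. **Is there a drug that differs by arm?** No. The abstract and the Interventions section give real herbal medicine to both groups, and no placebo herb is described. The formula varies with the patient's pattern, not with the arm.

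3. **Could the herbs be prepacked by allocation number?** Not as described. They depend on the pattern diagnosis, change weekly at the physician's discretion, come from the hospital and are decocted by the patient. If they were prepacked, they would carry no information about the arm.

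4. **What does differ?** The two intervention sections give:

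| Component | Overall adjustment group | Sham group |
|---|---|---|
| Body needles | 0.25 × 40 mm, manipulated to obtain *Qi* | 0.25 × 25 mm, blunt tip, no penetration or manual stimulation |
| Skin needle | *Qixing* needle, tapped to redness (petechiae in one pattern) | Tips wrapped in cotton |
| Cupping | Moving cupping until marks appear, then retained cupping | Smaller negative pressure |

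All three rows describe something an operator does. None is a drug.

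5. **Who must know the arm?** The acupuncturist, whom the article says cannot be blinded. The route by which the acupuncturist learns the assignment is therefore essential to concealment, and the drug-container sentence does not supply it.

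6. **Does the next sentence supply it?** Blinded researchers are to enrol and assign. That is coherent if they hand on a sealed, coded item that carries the treatment. It depends on the container device and cannot stand in for it.

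7. **Does the emergency code supply it?** No. It is for unblinding after a serious adverse event and plays no part in assignment.

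The mechanism and the intervention do not match at steps 2 to 5.

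**The case against.** The best defence is that drug is a slip of wording. The containers are said to hold investigational treatments. The abstract treats the herbs as basic treatment, and the blinding section speaks of investigational treatments where it means what patients are blinded to. The same company makes both the real and the blunt needles, so the manufacturer could be the needle maker supplying identically packed, numbered needle kits. Such kits would hide the arm until opened, and assigning the next number blind is exactly how that system works.

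This is plausible, and it rules out saying that the device conceals nothing or could never operate. But the article does not describe needle kits. A kit also would not set the cupping pressure: the operator would need an instruction, or would have to infer the arm from the needle, and neither is stated.

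A second defence is that a journal article may leave such detail to the full protocol. That excuses silence. Here the article names a mechanism, and the mechanism named does not fit.

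A reader might also infer that enrolling staff hold codes for patients not yet entered, and so could foresee allocations. The text does not support this. It describes restricted emergency disclosure. It does not identify the holders as the enrolling staff, say that the codes can be read at will, or say that they cover people not yet enrolled; and it calls the enrolling researchers blinded.

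Part of good practice is already present: an independent statistician makes the sequence, and the visit table puts consent, eligibility and BMD at month −1 and allocation at month 0.

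**Conclusion.** The point holds as a mismatch: the only concealment mechanism in the article is written for a drug comparison, and this trial randomises procedures carried out by unblinded operators. A reader or ethics committee cannot establish from this text that allocation was concealed.

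The sentence applies to all 104 planned allocations (52 per group). The size of any resulting bias cannot be calculated from the document, and none is shown to have occurred. A sound method may be in use and badly described. The conclusion assumes that the herbs are supplied as the Interventions section states, and that no unlisted drug differs between arms. It does not depend on who holds the emergency codes. It should be corrected because the safeguard is basic and the correction is cheap.

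**What to change.** Replace the drug-container sentence with a mechanism that fits the intervention:

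- Allocate centrally by telephone or web, or use sequentially numbered opaque sealed envelopes prepared from the independent statistician's list.
- Release each assignment only after consent, eligibility and baseline measures have been recorded, and only to the treating acupuncturist. It then covers needles, tapping and cupping together.
- State that emergency codes are held by someone not involved in enrolment or outcome assessment.

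If a suitable mechanism is already in use, such as sealed needle kits with an enclosed procedure instruction, describe it in place of the present sentence.

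The cost is a set of envelopes or a central service, and a one-paragraph amendment. The trial status section reports that recruitment had begun but was not complete, so a new procedure would cover only the remaining allocations. For those already made, the amendment should report how they were in fact assigned.

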### Sample size and blinding

According to the preliminary research [15], we hypothesize that the effective rate after OA is 77.8% and the effective rate after SA is 50%. The equation that we used for this was *α* = 0.05, *β* = 0.20 and we determined that a sample size of 42 patients in each group would be sufficient to detect the statistical difference between the two groups, allowing for a 20% withdrawal rate. We will plan to enroll a total of 104 participants with 52 participants in each group. According to the random number sequence generated by computer, the patients will be randomly divided into either the OA group or the SA group in a 1:1 ratio.

The participants, outcome assessors, study monitors, data managers, and statisticians will be blinded to treatment allocation. If possible, the study participants will be advised to avoid discussing the investigational treatments with other participants. Blinding will be maintained until the 104 participants have completed the study. The success of double-blinding will be assessed at the final visit. Due to the special nature of acupuncture, acupuncturists cannot be blinded to the treatment. The database will then be locked. An emergency code for each individual has been provided to the study researchers and will be disclosed only if it must be known whether a patient is receiving acupuncture treatment or SA in order to manage a serious adverse event.

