### Primary outcome

The primary outcome is BMD. BMD is measured using dual-energy x-ray (DEXA) absorptiometry (DMS, Paris, France; model: CHALLENGER C 313). A BMD measurement of the lumbar vertebrae (L1–L4) in the two groups will be measured before and after treatment.

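### The sample size rests on an undefined binary effective rate, so its 80% power does not apply to BMD, the primary outcome

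*Protocol article*

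**What the plan says.** Under Sample size and blinding, the protocol article takes its planning values from preliminary research: "we hypothesize that the effective rate after OA is 77.8% and the effective rate after SA is 50" per cent. It sets the error rates ("The equation that we used for this was *α* = 0.05, *β* = 0.20") and concludes that "a sample size of 42 patients in each group would be sufficient to detect the statistical difference between the two groups". With a withdrawal allowance of 20%, it arrives at the enrolment target: "We will plan to enroll a total of 104 participants with 52 participants in each group".

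Under Primary outcome, the article states "The primary outcome is BMD". This is a DXA measurement at L1–L4, taken before and after treatment. No threshold is given that would turn it into a success or failure for each patient.

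The Abstract, Table 3 and the outcome sections list the other measures: hormones, bone and oxidative markers, pathway proteins, pain VAS, TCM syndrome score, quality of life, and fractures at follow-up. None of them is an effective rate.

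**The concern.** A sample size calculation carries its power only to the comparison it was done for. Here that comparison is between two proportions of patients classed as effectively treated, while the comparison that decides the trial is between two groups on a continuous density measurement. The article offers nothing to bridge them: no definition of effective, no cut-off on BMD or any score, and no BMD difference or SD.

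A reader who sees 80% power in the sample size section and BMD as primary will naturally join the two. If the BMD result is then null, it may be taken as coming from a trial with known, adequate power for BMD. The article gives no basis for that.

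**Working it through.** **Inputs from the article (Sample size and blinding).** Rates 0.778 and 0.50; alpha 0.05, sidedness not stated; beta 0.20; 42 per group; 20% withdrawal; 52 per group enrolled; 1:1 allocation.

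**Step 1. Reproduce the stated number.** Two proportions, unpooled variance, two-sided 5%:

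n = [p1(1−p1) + p2(1−p2)] × (1.960 + 0.842)² / (p1−p2)²

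- Variance term: 0.778 × 0.222 + 0.50 × 0.50 = 0.4227
- (1.960 + 0.842)² = 7.849
- (0.278)² = 0.0773
- n = 0.4227 × 7.849 / 0.0773 = 42.9

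The stated 42 agrees to within rounding. For withdrawal, 42/0.8 = 52.5 against 52 enrolled, which also agrees to within rounding. The 80% power is thus identified as that of a test of 77.8% against 50%.

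**Step 2. Look for the effective rate among the outcomes.** The places checked were the Abstract, Table 3, Primary outcome, Secondary outcomes, Blood testing and Data analysis. The term is not defined or listed in any of them. Data analysis mentions a chi-square test in general terms and names no responder endpoint.

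**Step 3. What the planned numbers give for BMD.** The article supplies no BMD SD, target difference or baseline correlation, so everything here is in SD units and rests on assumptions: two-sample t-test, two-sided 5%, 80% power. Two group sizes are relevant:

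- 52 per arm, because Data analysis makes the intention-to-treat set primary and carries the last observation forward;
- 42 per arm, the number the sample size section expects after withdrawal (52 × 0.8 = 41.6).

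The normal approximation is (1.960 + 0.842) × √(2/n): 0.549 SD at n = 52 and 0.611 SD at n = 42. The t distribution raises these to 0.555 and 0.619. Adjusting for baseline BMD with correlation rho multiplies them by √(1−rho²), which is 0.866, 0.714 and 0.436 for rho 0.5, 0.7 and 0.9.

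| Analysis (assumed) | 52 per arm | 42 per arm |
|---|---|---|
| Unadjusted | 0.55 SD | 0.62 SD |
| Baseline-adjusted, rho 0.5 | 0.48 SD | 0.54 SD |
| Baseline-adjusted, rho 0.7 | 0.40 SD | 0.44 SD |
| Baseline-adjusted, rho 0.9 | 0.24 SD | 0.27 SD |

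Unadjusted power for an assumed true difference of 0.5 SD is 71% (52 per arm) or 62% (42 per arm). For 0.3 SD it is 33% or 27%.

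**The case against.** The strongest reply has four parts.

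- **The arithmetic is sound.** A reader might infer an error because a pooled-variance formula gives 46 per group, a continuity-corrected one gives 53, and 42/0.8 rounds up to 53 rather than 52. The article names no formula that would make 46 or 53 the right answer, and the withdrawal gap is half a patient per arm. This part of the reply stands in full.
- **The power for the stated proportions may be met.** At 42 per arm, exact power for 77.8% against 50% is 78% (Pearson chi-square) or 71% (Fisher). At 52 per arm, the intention-to-treat number, it is 86% or 80%. So it cannot be said that the design misses its own 80% on its own terms.
- **The trial may not be underpowered for BMD.** A reader might infer that it is, from the 0.62 SD figure. That figure assumes 42 per arm and no use of the baseline scan. BMD is measured before and after treatment, and the detectable difference falls sharply as the assumed correlation rises. The documents show that the power for BMD is unstated, not that it is low. Carrying observations forward could dilute a true effect, so 52 per arm is the favourable end.
- **The effective rate may be defined elsewhere.** The article is condensed, cites preliminary research for the rates, mentions a chi-square test and introduces its secondary outcomes as an inclusive list. It would therefore go too far to say that no such test will ever be run. What can be said is that the article does not define or list the rate. Even a definition elsewhere would not turn this calculation into one for BMD.

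None of the four supplies a link between the effective rate and BMD.

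**Conclusion.** The point holds as a mismatch between the sizing endpoint and the primary endpoint. The figures of 42 per group, 52 enrolled and 80% power belong to a binary quantity that the article neither defines nor lists. They do not apply to L1–L4 BMD, for which no power is stated. The calculation itself is not at fault.

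The size cannot be fixed from the article. On the stated assumptions, the detectable BMD difference at 80% power runs from about 0.24 SD (52 per arm, rho 0.9) to 0.62 SD (42 per arm, unadjusted). That range is too wide to call the trial adequately powered or underpowered for BMD. The paragraph should be corrected because it gives the reader a power figure for a different comparison from the one that decides the trial.

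**What to change.** Keep 104 participants and rewrite the sample size paragraph in two parts.

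1. Say plainly that the number was chosen from an effective rate of 77.8% against 50%, and that this does not give the power for BMD. If the effective rate is meant to be analysed, define it and list it as a secondary outcome.
2. State the difference in L1–L4 BMD, in g/cm², that the trial can detect with 80% power at two-sided 5%. Use the SD and baseline correlation the sponsor holds, give the figure for 52 and for 42 per arm, and say whether the analysis adjusts for baseline. Until those inputs are filled in, the SD-unit table above can serve as the range.

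The cost is one reworded paragraph and no extra patients. The downside is that the stated power becomes less favourable: a single 80% claim is replaced by a detectable difference that readers can judge for themselves.
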